### *HABIT-ILE procedure*

HABIT-ILE is a **motor skill learning-based therapy carried out in a camp-setting, with structured tasks of increasing motor difficulty and functional activities that require the use of both hands whilst sustaining postural or locomotor activity of the LE**. Tasks are based on games and the whole environment is set up such that the children perceive the camp as fun. For both the children with unilateral

and bilateral CP, the tasks will be chosen according to individualized functional goals previously defined by the parents (e.g. drinking by him/herself, walking without help, opening a box of toys, holding a book, putting off pants, playing in sitting without support, etc.). Results of the initial assessments (T0) will be used to determine appropriate tasks for each child. Over the course of the 2 weeks, tasks will be progressed to further challenge bimanual coordination, postural control and LE function. Initially, the more affected upper extremity (UE) will be used as a passive stabilizer, with progressive encouragement towards more complex (active) use of this hand by introducing games that require more skilled use of the more affected UE. LE/postural involvement in the different tasks/activities will also be progressively more demanding: 1) sitting activities (initially on a chair or a mat potentially with a back support, progressing towards unsupported sitting and sitting on unstable supports e.g. roller or ball), 2) transitions from lower to higher postures using the UE for support, 3) stable gross motor activities (from standing with UE support to playing during free standing) and 4) movement activities (crawling, walking, running or jumping), with graded difficulty. More skilled/challenging UE activities will be systematically introduced in stable sitting and the child will be subsequently challenged to perform the UE activity in more challenging LE conditions. More challenging LE/postural conditions will also be progressively introduced while performing a bimanual task that has already been mastered.

Although the basic principles of HABIT-ILE will be followed, the toys, tasks and activities will be adapted so that only bimanual use will be possible. Babies and very young children can perform bimanual activities (bimanual reaching, holding, transfer, symmetrical and asymmetrical actions) at one year old. However this requires the use of specific toys that afford bimanual use through their characteristics: e.g. for bimanual reaching / holding, use of a tool that is too big, too heavy or not stable enough to be picked up with one hand. The duration of activities as well as LE/postural associations will also be adapted to each child depending on his/her functional objectives, attentional ability and gross motor development. The whole process will be performed in a **child-friendly, fun environment adapted to the age of the child**.

**Eight children will undergo rehabilitation together.** Some activities will be carried out in groups and others individually. Each child will have his/her own therapist (PT or OT) as well as a student therapist working with him/her. The aim is to maintain a structured motor engagement time of 80 % throughout the 10 days of therapy. The post-doctoral scientist dedicated to the project will supervise all camps in order to standardize the procedures and train all therapists and students.

Since previous intensive treatments delivered by parents or at home with videos/online supervision have so far been disappointing, both regarding compliance with guidelines and the moderate motor changes observed, the highest feasible intensity treatment will be delivered in this study. **Recent studies on dosage support that 50 to 60 hours of intensive therapy are needed to induce motor changes**. Taking into account usual motor activity time and rest time (e.g. naps), 5 hours per day for a total of 50 hours is the best compromise between current scientific evidence on dosage and the number of feasible hours in this age group. This amount of therapy time is close to the CIMT trial that has provided the greatest effectiveness.

**The adaptation of HABIT-ILE to pre-school children is based on the know-how developed in school-age children** and a pilot camp will be performed in the second trimester of 2018 in Brussels in pre-school children (prior to the start of this project). The aim of the pilot camp is to develop and test a standardized therapeutic procedure before implementation in the multicentre study in Brussels, Pisa, Brest and Angers.

### *Control procedure*

The control procedure consists of the child's usual activity, including nursery, usual rehabilitation, etc. The spontaneous activity of preschool children is usually oriented towards the discovery of their environment. A recent study based on accelerometers demonstrated that toddlers spend around 7.6 hours/day carrying out motor activities. Since a proportion of these activities are performed at home, before or after going to the nursery/preschool (i.e. dressing in the morning, taking a bath, having dinner or brushing teeth before sleeping), excluding nap time, thus around 5 hours of daily motor activity were estimated to be carried out in nursery. The **content of the activity** will be documented by the person in charge (notebook) and the **amount of activity will be documented objectively by wearable sensors** (see WP 3). This control 'intervention' condition was chosen as the comparison group because it represents the current model of rehabilitation in many countries. The choice of **this control group is highly clinically relevant because it compares a new model of rehabilitation to the current on-going model of rehabilitation in many countries**. It also allows the comparison of the "structuration" of motor activities and "spontaneous activities" to be carried out.

### *Evaluation criteria*

In each RCT, both groups (N=25) will be assessed 3 times: T0, T+15 days and T0+90 days (See study design in Figure 4).

For the RCT 1, the primary outcome measure will be the difference in the **Assisting Hand Assessment (AHA, from 18 months to 18 years) or Mini Assisting Hand Assessment** (Mini-AHA, from 8 to 18 months) between T0 and T0+90 days. It quantifies through a Rasch analysis the assistance that the more affected hand can provide to the less affected hand in bimanual activities. This primary outcome was chosen because 1) it has become the gold standard measure of bimanual performance in children with unilateral CP 2) its **responsiveness, reliability and validity** have been demonstrated in children with CP including infants and toddlers. 3) its raw scores are transformed through a rash-model into linear measures, allowing the use of parametric statistics 4) the assessment can be **videotaped and scored by a trained examiner totally blind** to group assignment and timing of assessment ensuring a blind scoring, which is planned for this study. The minimal detectable change is 4 AHA-Units (0.97 logits).

For the RCT2, the primary outcome measure will be the difference in **Gross Motor Function Measure GMFM (in% of logits) between T0 and T0+90 days**. The GMFM is a clinically validated tool designed to evaluate changes in gross motor function over time or following an intervention in children with cerebral palsy. It includes 66 items identified through **Rasch analysis** that best describe gross motor function in children with cerebral palsy of varying abilities. The items cover a large spectrum ranging from activities in lying and rolling to walking, running and jumping. This primary outcome was chosen 1) because it can be performed both in preschool and school-age children, allowing a sample size calculation based on previous data in school-age children; 2) its **responsiveness, reliability and validity** have been demonstrated in children with CP including infants and toddlers; 3) its raw scores are transformed through a rash-model into linear measures, allowing the use of parametric statistics; 4) the assessment can be **videotaped and scored by a trained examiner totally blind** to group assignment and timing of assessment ensuring a blind scoring, which is planned for this study. The blinded examiners of the consortium will be trained and their inter-examiner reliability will be tested by scoring videos of the same children. Finally, the developmental curves for the GMFM-66 are known for children with different levels of GMFCS allowing **significant clinical change to be differentiated from the normal physiological evolution of the child**. The minimal detectable change is 2 logits.

**The secondary outcomes will be investigated at T0, T+15 days and T0+90 days and are specified in the description of each work-package.** The **3 levels of the International Classification of Functioning, Disability and Health (ICF)** will be systematically evaluated for each child in order to track changes at the body level (e.g., assessing manual ability), activity level (using questionnaires) and at the level of social participation (using questionnaires)(See WP 1,2,3). **Although the number of assessments might seem quite high for children of this age, the estimated time to carry out the full assessment is < 2 hours for the functional assessment of the GMFM/AHA + evaluation criteria of WP1, 30-45 minutes for WP2 (MRI) and 30-45 minutes for WP3 (3D Movement analysis).** The evaluation will be carried out over a day to allow the children to have free activities in between each test.

#### *Statistical analysis: sample size and statistical analysis of the main primary criteria*

Unilateral CP (RCT1): The sample size was calculated based in one study performed in infants and young children (Eliasson & al., 2011). This study evaluated the effect of eco-Constraint Induced Movement Therapy (Eco-CIMT) using a cross-over design. They showed an improvement of 6 units in the AHA (Main outcome, Minimal detectable change of 4 AHA-unit) for the intervention group and a change of 2 units in the control group. In our study, we expect at least an improvement of 6 units after HABIT-ILE in a similar population in term of age. In addition, the effect size estimated in Eliasson's study was of 1.26 unit. With these results, and with an  $\alpha=0.05$  and a  $1-\beta=0.9$ , a sample size of 15 participants per group would be required, with a total of 30. The results obtained by Eliasson are consistent with the results of our pilot study evaluating HABIT-ILE in 10 children with unilateral CP (ages between 1 and 4 years old), where the mean improvements observed in the AHA at 3 months was of 10 units with a SD of 6.7 (Personal data). To take into account the differences between the populations and interventions and to be cautious regarding the variability of our targeted population, our hypothesis is an effect size of at least 1 unit (i.e., an improvement of 1 SD in the HABIT-ILE group when compared with the control group) with an  $\alpha=0.05$  and a  $1-\beta=0.9$ . Therefore, for the sample size, 23 participants per group are required, with a total of 46. Considering potential drop-outs, **50 participants will be included in total.**

Bilateral CP (RCT2): The sample size was calculated based on the mean improvement observed in the GMFM in [name] et al., (2017), where the intervention group (HABIT-ILE) showed an improvement of 7 logits (Minimal detectable change=2 logit) and the control group showed a change of 2 logits in the same time period (3 months). To take into account the differences between the populations and to be cautious regarding the variability of our targeted population (younger pre-school infants), we consider that the SD of

improvement could reach at the most 5 logits. Then, we hypothesize a difference between both groups of 5 logits and a SD of improvement of 5 logits with an  $\alpha=0.05$  and a  $1-\beta=0.9$ . With these hypothesis, a sample size of 23 participants per group is required, with a total of 46 participants. Considering potential drop-outs, **50 participants will be included in total.**

Improvements in GMFM and AHA will be compared between study groups using analysis of covariance (ANCOVA) to adjust for baseline measurement (as described and recommended in Vickers et al.) Non-parametric methods will be performed whenever ANCOVA assumptions (homoscedasticity, normality) are not met. Age-subgroup (or according to other characteristics) and interaction analyses will be performed for exploratory purpose. As recommended by Good Clinical Practice, exploratory analyses will be used for hypothesis generating but cannot be conclusive alone. The statistical analysis of the secondary outcome measures are described in the relevant WPs. Secondary outcome analysis, as well as subgroup analysis, should be considered as exploratory unless using specific methods in order to control the Type I error probability (multiplicity problem).

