### *Design and Randomization*

This project will involve **2 single-blind randomized controlled trials (RCTs), one with children with unilateral CP and the other with children with bilateral CP**. The decision to carry out two separate RCTs was made by the consortium and methodologist based on the fact that the causes, and most importantly for this project, the functional motor outcomes and rehabilitation goals differ for these two CP types. For each RCT, the randomisation will be carried out 24 hours per day using centralised computer randomisation by internet. A **pair-matched randomization** will be used in order to ensure comparability. For children with unilateral CP, each child will be matched with a child with the closest profile based on age (4 categories: 1,2,3,4 yo), the affected side (right or left), and the origin of the CP (prematurity, perinatal asphyxia, stroke, others). For children with bilateral CP, each child will be matched with a child with the closest profile based on age (4 categories: 1,2,3,4 yo), the Gross Motor Function Classification System level (GMFCS, 3 categories: I-II, III-IV and V) and the origin of the CP (prematurity, perinatal asphyxia, stroke, others). All the efforts will be made in both RCTs to find the closest profile within the same year, same GMFCS level and same origin of CP. Group allocation will be then randomly determined within each pair. This design was chosen to limit the heterogeneity in clinical pattern between the intervention and control arms, while keeping the benefit of individual randomization. It is commonly used and widely accepted in the field of neuropsychiatric rehabilitation. The 2 trials will also be equilibrated according to the age groups 1-2 (50% of the group) and 3-4 (50% of the group) in order to investigate the effect of window of opportunity.

In both RCTs (unilateral and bilateral), the children will be randomized to receive HABIT-ILE or the Control condition. The children in the control group will receive the therapy after the 3 month follow-up assessment in order to decrease drop-out at follow-up in this group, however, this will not be included in the analysis. Thus the between group comparisons will be carried out between T0 and T+15 and between T0 and T+90. The design of RCTs 1 and 2 is presented in Annex.

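### Both trials randomise within matched pairs, but the stated primary ANCOVA carries neither the pair nor the matching factors, so its standard error is overstated to the extent that pair-mates' outcomes remain correlated after baseline adjustment

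*Protocol*

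**What the plan says.** Protocol section 2.3, Design and Randomization, sets up pair matching in both trials. RCT1 pairs children on age category, affected side and origin of the CP. RCT2 pairs them on age category, GMFCS band and origin. Then "Group allocation will be then randomly determined within each pair". The reason given is that "This design was chosen to limit the heterogeneity in clinical pattern between the intervention and control arms".

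The subsection on sample size and statistical analysis of the primary criteria states the primary analysis: "Improvements in GMFM and AHA will be compared between study groups using analysis of covariance (ANCOVA) to adjust for baseline measurement". It names no pair effect and no matching factor. The fallback is equally silent on pairs: "Non-parametric methods will be performed whenever ANCOVA assumptions (homoscedasticity, normality) are not met". Age enters only through exploratory subgroup and interaction analyses.

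The sample size in both trials rests on a standardised difference of 1. For RCT1, "our hypothesis is an effect size of at least 1 unit", explained there as 1 SD. For RCT2, "we hypothesize a difference between both groups of 5 logits and a SD of improvement of 5 logits". Each gives 23 children per group, raised to 25 for drop-out.

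**The concern.** Randomising within pairs changes the sampling variance of the treatment difference. If two children in a pair tend to do well or badly together for reasons that the baseline score does not capture, that shared component cancels between the arms. A two-group ANCOVA leaves it in the residual variance, so the model reports more uncertainty than the design produces.

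At stake are interval width and the chance of detecting an effect smaller than planned. Each trial has only 50 children, and section 3 says that a negative result would itself be used to discourage intensive treatment. Leaving the matter open also carries a risk: choosing between a paired and an unpaired analysis after unblinding could change the P value.

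**Working it through.** **1. The plan's own figure.** Inputs from the protocol: standardised difference 1, alpha 0.05, power 0.90. The normal approximation for two independent means gives 2 × (1.960 + 1.282)² / 1² = 21.0, or 22 per arm after rounding up. The two-sided t-test calculation gives 22.02, rounded up to 23, which matches. A one-sided t-test gives 18 and does not match. The sizing therefore treats the arms as independent groups and takes no credit for matching.

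**2. Standard error.** Let rho be the within-pair correlation of outcomes after baseline adjustment, sigma the residual SD and m the number of pairs. The protocol gives no rho; 0 to 0.5 is an assumption.

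- SE reported by a model that ignores pairs: sigma × sqrt(2/m)
- True SE under within-pair allocation: sigma × sqrt(2(1-rho)/m)
- Ratio: 1/sqrt(1-rho)
- Actual two-sided type I error: 2 × (1 - Phi(1.96/sqrt(1-rho)))

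With m = 23 and sigma = 1, the reported SE is sqrt(2/23) = 0.295 at every rho. At rho 0.3 the true value is 0.295 × sqrt(0.7) = 0.247.

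| rho | SE ratio | Type I error, formula | Type I error, simulated |
|---|---|---|---|
| 0 | 1.00 | 0.050 | 0.051 |
| 0.1 | 1.05 | 0.039 | 0.042 |
| 0.2 | 1.12 | 0.028 | 0.031 |
| 0.3 | 1.20 | 0.019 | 0.021 |
| 0.5 | 1.41 | 0.006 | 0.008 |

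The simulation used 23 pairs and 8,000 runs per setting. The mean SE reported by the baseline-only ANCOVA was about 0.294 throughout, while the estimate's true sampling SD fell from 0.30 at rho 0 to 0.25 at 0.3 and 0.21 at 0.5. A baseline-adjusted within-pair analysis kept its type I error between 0.048 and 0.051.

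**3. Power.** Same simulation, baseline-only ANCOVA against within-pair analysis. The 0.7 SD effect is an assumption; the protocol plans for 1 SD.

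| rho | 1 SD, ANCOVA | 1 SD, paired | 0.7 SD, ANCOVA | 0.7 SD, paired |
|---|---|---|---|---|
| 0 | 0.908 | 0.883 | 0.646 | 0.608 |
| 0.1 | 0.928 | 0.919 | 0.633 | 0.636 |
| 0.2 | 0.935 | 0.947 | 0.657 | 0.705 |
| 0.3 | 0.945 | 0.965 | 0.665 | 0.761 |
| 0.5 | 0.966 | 0.993 | 0.686 | 0.875 |

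With 25 pairs, an assumed effect of 0.6 SD and rho 0.3, power is about 55% for the ANCOVA and 66% for the paired analysis.

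**4. Limits of the check.** These gains come from modelling the pair alone. If the matching factors enter as fixed effects, they absorb part of the correlation they cause, and a pair term on top may add less than the table shows.

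**The case against.** The strongest reply is that everything turns on a correlation the protocol does not report. The supporting evidence is thin. The Evaluation criteria section says that GMFM developmental curves are known by GMFCS level. That bears on RCT2 and one matching factor, and does not show that the factor predicts three-month change once baseline GMFM is in the model. For RCT1 there is no comparable statement about the AHA. Matching is approximate, to the closest available profile with broad GMFCS bands. A rho near 0 is therefore possible, and there the stated ANCOVA is correct and slightly more powerful than a strictly paired analysis. This stands, and it is why the size is given as a range that starts at zero.

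A second reply is that the covariate list belongs in a statistical analysis plan, which is not at hand. This stands only in part: the protocol does not exclude further terms, but it does name the model and its covariate, and that statement leaves out the randomisation structure.

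Three stronger readings are tempting and not supported:

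- A reader might infer that both trials' standard errors are certainly too large. That needs a positive residual correlation, which the document does not establish.
- A reader might infer that the benefit of matching is lost. The stated purpose is comparability of the arms, which any analysis keeps, and the estimate's true variance still falls. Only recognition of that precision in the SE, interval and P value is missing.
- A reader might infer that the trials are underpowered or exposed to false positives. The sample size never relied on matching, and the error is conservative.

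**Conclusion.** The point holds as a mismatch between design and stated analysis, in both trials. The treatment estimate is not biased and the type I error is not inflated. If rho lies between 0.1 and 0.3, the reported standard error is about 5% to 20% too large; at 0.5 it would be 41% too large, and at 0 there is no error. These figures assume a common within-pair correlation, equal residual variance in the arms and complete pairs.

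At the planned 1 SD the stated analysis keeps at least 90% power with 23 complete pairs. The practical loss is for smaller effects with moderate rho: about 10 percentage points at 0.7 SD and rho 0.3 (0.665 against 0.761). This should be fixed, but it does not threaten the validity of a positive result.

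**What to change.** Amend the primary-analysis paragraph of the statistical analysis subsection, for both trials:

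- Make the primary model a linear mixed model or ANCOVA of change from T0 to T0+90 days with arm, baseline score and a pair effect. A random intercept for pair is preferable, because a child whose pair-mate drops out then stays in the analysis.
- Add a within-pair re-randomisation test as the supporting analysis. It guards against small-sample error in the mixed model: in one simulation with 25 pairs and rho 0, the random-intercept model rejected a true null 0.066 of the time, against 0.060 for ANCOVA in the same runs.
- Make the non-parametric fallback pair-based.
- As an acceptable minimum, adjust for the matching factors: age, origin of CP, and affected side (RCT1) or GMFCS category (RCT2).
- Settle the choice before unblinding.

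The cost is wording: the pairs and matching factors are already recorded at randomisation. The statistical price is a few degrees of freedom. A strictly paired analysis would lose a little power if rho is near zero (0.883 against 0.908 at 1 SD).

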#### *Quality procedure*

A clinical research assistant employed by the promoter will ensure the quality of the study, the data collection, documentation and recording etc., in accordance with the Standard Operating Procedures in Brest CHRU, Good Clinical Practice and current legislation. A web-based interface will be created for randomization, and an electronic case report form will be set up to collect all study data.

